#### Inclusion criteria

2.4.3

(1)Age 18 to 85 years old;(2)Met the criteria of Sepsis 3.0^[20]^, which defines sepsis as infection + sequential (sepsis) organ failure assessment score (SOFA) ≥ 2 points within the first 24 hours;(3)First ICU admission and the patient should be expected to survive within the first 48 hours;(4)Informed consent was signed by the patient or their next to kin;(5)The RF_CSA_ decreased more than 9.24%^[21]^ after ICU admission;(6)Alive during the ICU stay.

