#### Exclusion criteria^[1,2]^

2.4.4

(1)A confirmed pregnancy or the urine β-HCG test is positive;(2)The questionnaires (MRC-SS and FIM^TM^) or consent form could not be completed due to cognitive abnormalities.(3)A newly diagnosed primary neuromuscular disease when admitted to the hospital;(4)Leg amputation, pelvic/femoral fractures or knee/hip replacement that prevent the measurement of the RF_CSA_;(5)Malnutrition (BMI less than 18.5 kg/m^2^) or cachexia;(6)Metastatic tumors (PD) or ongoing chemotherapy;(7)Cardiorespiratory arrest or imminent death;(8)Long-term corticoid treatment;(9)Could not walk independently before sepsis onset;(10)ICU length of stay (LOS) < 7 days^[2]^;(11)Sepsis onset more than 5 days before ICU admission^[2]^;(12)Therapy withdrawal or consent refusal.

Patients are eligible if they are diagnosed with sepsis, their RF_CSA_ decreased more than 9.24%^[21]^ from baseline, and informed consent has already acquired from the patient and/or immediate family member. A case report form (CRF) will be completed, and the RF_CSA_, MRC-SS score and other relevant data will be obtained, for all eligible and consenting patients. We will use the RF_CSA_ to assess the changes in muscle morphometry; the MRC-SS will be used to assess whether patients meet the diagnostic criteria of ICU-acquired weakness and to observe mortality, rehospitalization, reintubation and mechanical ventilation and other relevant indicators during the 1-year follow-up.

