#### Acupuncture treatment

2.5.1

According to the patient's (and/or their relatives’) willingness and the clinical routine, a group of physicians will assess the acupuncture treatment within 24 hours in patients who meets the inclusion criteria 1 to 5. All physicians are required to have at least 3 years (or 300 hours) of practical experience with acupuncture. The acupuncture treatment will be performed by stainless steel needles (0.30 mm × 40 mm; 0.30 mm × 25 mm; Suzhou Medical Supplies Factory Co., Ltd., Suzhou City, China). The acupuncture treatment will be performed by the technique of lifting, thrusting, twirling and rotating the needle until the patient is being “De-qi” (getting a numbness or other acupuncture feeling). Two points that do not cross the joint will be chosen for electrical stimulation. The needle will be kept in place for approximately 30 minutes. By the time we remove the needles, a clean cotton balls will be pressed to the skin to prevent bleeding.

All patients must be treated at “3 obligatory basic acupuncture points”: ST36, ST40 and LI10. Furthermore, at least 3 additional acupuncture points will be selected according to the principles of traditional Chinese medicine (for example, if the patient has a mental disorder manifestation, acupoints such as GV20, GV24, and EX-HN3 can be added to promote the patient's waking). Additional acupoints could be applied, and ear acupuncture points might also be included. All acupoints selected in each session will be recorded. A traditional Chinese syndrome diagnosis is required, and the diagnosis will be documented. Acupuncture treatment will be performed twice a day and lasts for 30 minutes. If the included subjects do not meet the exclusion criteria and do not terminate their participation in study, they will receive acupuncture treatment during their entire ICU stay. If the patient is discharged from the ICU, the acupuncturist will continue to follow the patient until the 14-day acupuncture session is completed. Both the acupuncture group and the control group will receive basic sepsis treatment. The selection of acupuncture points is listed in Table 1.

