### Study groups

2.7

Since this study is a real-world study, the grouping of the study subjects was determined by the actual observations. Therefore, no randomization of groups was set in this study. The subjects will be as allocated into 2 arms.

Group 1: acupuncture group

When the participant meets the inclusion criteria (1 to 5), the acupuncturist will assess the conditions for patient treatment. Patients can enter this group and have acupuncture treatment if they do not have specific conditions (such as edema, coagulopathy, acupoints local skin and soft tissue infection, and rejection of acupuncture treatment) that are not suitable for acupuncture.

Group 2: control group

Patients who are not suitable for acupuncture or are not willing to receive acupuncture could enter this group. In addition to basic treatment, patients in this group will be prescribed exercises, such as early in-bed activities or wheelchair activities.

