### Outcome

2.8

The primary outcomes will be the decline of RF_CSA,_ the MRC-SS and time-to-event (defined as all-cause mortality or unplanned readmission to the ICU due to invasive ventilation). The activities of daily living will be accessed by the motor item of the Functional Independence Measure (FIM^TM^). Secondary outcome includes the expression level of MSTN, ICU length of stay, length of hospital stay, duration of invasive/non-invasive mechanical ventilation. The outcomes will be measure as follow:

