#### Collecting healthcare data within the ICU stay

2.8.6

During the screening period, the relevant subject information will be completed, and baseline demographic-related items will be collected. The SOFA score, the immediate acute physiology and chronic health evaluation II score (and SAPS score), the GCS score, body temperature, mechanical ventilation or not, the infection site, the pathogenic examination before the administration of antibiotics or use of vasoactive drugs, arterial blood gas analysis, blood routine, coagulation function, liver function, kidney function, heart function, infection index, urine pregnancy test (female subjects), and an electrocardiogram will be recorded during this period. The length of the first antibiotic use and whether the pathogen is sensitive to the antibiotic will be recorded after initiation.

For patients who survive and are discharged from the ICU - meeting all inclusion criteria (1 to 6) - the mechanical ventilation duration time, LOS, total hospital stay, sum sedative analgesic dose, statin dose, blood glucose level, insulin dosage, glucocorticoid dosage, protective constraints, and the duration of neuromuscular blockers will be additionally recorded.

Table 2 shows a general view of the data collecting and the time of acquisition for each item. We will manage all study data anonymously, and all CRFs will be labelled with a study number allocated to each individual participant. The CRF will be in both paper and electronic formats. The paper version of the CRF will be used for backup storage of data and for verification when needed. The daily management of data will be completed on the EDC system. And the details of bedside data collection are shown in Table 3.

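### Exclusions (7) and (12) have no time limit and can be met after group entry, and nothing says such patients stay in a time-to-event analysis that counts death

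*Protocol article*

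**What the plan says.** All references are to the Protocol article.

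- **2.4.4 Exclusion criteria.** Item (7) is "Cardiorespiratory arrest or imminent death" and item (12) is "Therapy withdrawal or consent refusal". Neither states when it is assessed. Items (3), (9) and (11) in the same list are tied to hospital admission, sepsis onset and ICU admission respectively. Item (10), "ICU length of stay (LOS) < 7 days", can be settled only at ICU exit or day 7.
- **2.7 Study groups.** Group entry precedes full inclusion: "When the participant meets the inclusion criteria (1 to 5), the acupuncturist will assess the conditions for patient treatment".
- **2.5.1 Acupuncture treatment.** Acupuncture through the ICU stay is conditional: "If the included subjects do not meet the exclusion criteria and do not terminate their participation in study".
- **2.4.3 and 2.8.6.** Inclusion (6) is "Alive during the ICU stay". Further data are collected "For patients who survive and are discharged from the ICU - meeting all inclusion criteria (1 to 6").
- **2.8 Outcome and 2.10.** One primary outcome is "time-to-event (defined as all-cause mortality or unplanned readmission to the ICU due to invasive ventilation"), with time points counted from ICU admission.
- **2.8.7 Patient follow-up.** Follow-up runs to its scheduled end or to death. The exits named are a patient's refusal to continue and repeated failure of contact.
- **2.13 Adverse events.** If a change in condition means that the treatment plan must be stopped or altered, the subject leaves the study, not only the treatment.

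**The concern.** Arrest, a moribund state and withdrawal of therapy often come shortly before death. If meeting one of these after group entry takes a patient out of the study, the primary outcome loses deaths just before they would be counted.

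The loss need not be equal in the two groups. Allocation is not randomised, and critical care providers know the group. The sentence that applies the exclusion list to included subjects concerns acupuncture recipients. The adverse events listed in 2.13 are all complications of needling, so that exit is open mainly to the acupuncture group. Propensity-score matching on prognostic factors cannot bring back patients who were dropped after entry.

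**Working it through.** **1. Order of events.** Screening is within 24 hours of ICU admission (2.9). Inclusion (5) requires a fall in rectus femoris area of more than 9.24% from baseline. Scans are on days 1, 3, 5, 7, 10 and 14 (2.8.1), so the fall can generally not be shown before the second scan. Group entry follows, on criteria 1 to 5. Items (7) and (12) can first be met after that, and ICU deaths fall inside an outcome window that opens at ICU admission.

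**2. What happens to a patient who meets (7) or (12) after group entry.**

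| Section | Effect on treatment | Effect on study membership |
|---|---|---|
| 2.4.4 | none stated | excluded; no time given |
| 2.5.1 | acupuncture no longer assured | not stated |
| 2.13 | plan stopped or changed | withdrawn from the study |
| 2.8.7 | none | followed to death or end of follow-up; (7) and (12) are not among the exits |

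These sections do not give one answer, and none says that the patient stays in the time-to-event analysis.

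**3. The plan's own figures.** These fix only the group size used below. With 12.5% vs 39.3%, two-sided 0.05, power 0.80 and unpooled variance:

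n = (1.960 + 0.842)² × (0.125 × 0.875 + 0.393 × 0.607) / 0.268² = 38.02, rounded up to 39, as stated in 2.3.

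39 / (1 − 0.20) = 48.75, rounded up to 49. The 20% is inferred, since 2.3 gives no dropout rate. The point does not depend on either figure.

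**4. Illustration of size.** The documents give no mortality rate and no rate of exclusion after entry. Assume the same true event risk p in both groups, and that a share f of the patients with events is removed from one group only. Then in that group:

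observed risk = p(1 − f) / (1 − pf)

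false risk ratio = (1 − f) / (1 − pf)

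| p | f = 10% | f = 25% | f = 50% |
|---|---|---|---|
| 20% | 0.90/0.98 = 0.92 | 0.75/0.95 = 0.79 | 0.50/0.90 = 0.56 |
| 30% | 0.90/0.97 = 0.93 | 0.75/0.925 = 0.81 | 0.50/0.85 = 0.59 |
| 40% | 0.90/0.96 = 0.94 | 0.75/0.90 = 0.83 | 0.50/0.80 = 0.625 |

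At p = 30% the observed risks are 27.8%, 24.3% and 17.6%. The ratios favour the group that loses the patients. If the other group lost them, the ratios would invert: at p = 30%, 0.97/0.90 = 1.08 to 0.85/0.50 = 1.70.

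**5. Equal removal in both groups.** With equal true risks this creates no false difference, but it costs events. At p = 30%, 98 × 0.30 = 29.4 events fall to 26.5, 22.0 and 14.7 for f = 10%, 25% and 50%. By Schoenfeld's formula, power = Φ(√(events/4) × |ln HR| − 1.96). For an assumed hazard ratio of 0.5 this falls from 47% to 43%, 37% and 26%.

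**The case against.** Four counter-arguments have weight.

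- **2.5.1 concerns treatment.** Its consequence is continued acupuncture, and it names ending participation as a separate condition. A reader might infer that it expels patients who arrest or are dying. It does not say so. What stands is that it uses the trial's exclusion criteria as the test, and that 2.13 treats a stopped plan as leaving the study.
- **2.8.7 points towards retention.** It names neither (7) nor (12) as an exit. That is the best evidence against the concern. It does not settle whether someone who meets an exclusion is still a study patient to whom the rule applies.
- **A screening reading is natural.** Imminent death echoes the expected 48-hour survival in inclusion (3), and consent refusal belongs to entry. But item (10) shows that the list is not purely a screening list. The flowchart and timeline, which might settle the timing, are not shown in the text at hand.
- **Inclusion (6) already removes ICU deaths.** Most patients who arrest or become moribund in the ICU would presumably be lost through (6) anyway. This is correct and limits the separate effect of (7) and (12).

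A reader might also take therapy in (12) to mean acupuncture, so that only one group could meet it. The documents do not support this: the list covers both groups, and 2.7 places patients unwilling to have acupuncture in the control group. Nor can a particular false-positive rate or direction of bias be claimed, because any such figure needs removal shares by group that appear nowhere.

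**Conclusion.** The concern holds as a defect in the rules, not as a demonstrated bias. Items (7) and (12) have no time limit, can be met after group entry, and come close to an event that a primary outcome counts. The sections on treatment, adverse events and follow-up leave it open whether such a patient is kept. Selective loss is therefore permitted, possibly unequal between groups.

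Its size cannot be computed from the documents. The range of 0.93 to 0.59 at a 30% risk rests on three assumptions: equal true risk, removal from one group only, and removal shares of 10% to 50% chosen for illustration. The shares apply to all events up to 1 year, whereas removal in the ICU would mostly not reach later deaths and readmissions. Part of the effect also belongs to inclusion (6). The figures show sensitivity and are not an estimate.

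**What to change.** 1. In 2.4.4, state that (7) and (12) are assessed only up to the group decision, that is, when criteria 1 to 5 are met and the group is recorded.
2. In 2.5.1 and 2.13, state that meeting an exclusion, or stopping study treatment, after that decision ends neither follow-up nor inclusion in the time-to-event analysis. The patient is analysed in the recorded group, and a later death counts as an event.
3. In 2.8.7, state that only withdrawal of consent to data collection ends follow-up by decision. Loss of contact remains loss to follow-up.
4. Reconcile these statements with inclusion (6) and exclusion (10). If (6) stays as it is, the first three changes restore few ICU deaths, and counting a later ICU death would contradict (6).

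Whether acupuncture itself continues in such a patient is for the investigators and is not part of this change.

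The cost is a few sentences of protocol wording. Deaths and readmissions are already follow-up items, so no new type of data is needed, but patients who would have been withdrawn must now be followed. Observed mortality may be somewhat higher.

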### Intervention

2.5

#### Acupuncture treatment

2.5.1

According to the patient's (and/or their relatives’) willingness and the clinical routine, a group of physicians will assess the acupuncture treatment within 24 hours in patients who meets the inclusion criteria 1 to 5. All physicians are required to have at least 3 years (or 300 hours) of practical experience with acupuncture. The acupuncture treatment will be performed by stainless steel needles (0.30 mm × 40 mm; 0.30 mm × 25 mm; Suzhou Medical Supplies Factory Co., Ltd., Suzhou City, China). The acupuncture treatment will be performed by the technique of lifting, thrusting, twirling and rotating the needle until the patient is being “De-qi” (getting a numbness or other acupuncture feeling). Two points that do not cross the joint will be chosen for electrical stimulation. The needle will be kept in place for approximately 30 minutes. By the time we remove the needles, a clean cotton balls will be pressed to the skin to prevent bleeding.

All patients must be treated at “3 obligatory basic acupuncture points”: ST36, ST40 and LI10. Furthermore, at least 3 additional acupuncture points will be selected according to the principles of traditional Chinese medicine (for example, if the patient has a mental disorder manifestation, acupoints such as GV20, GV24, and EX-HN3 can be added to promote the patient's waking). Additional acupoints could be applied, and ear acupuncture points might also be included. All acupoints selected in each session will be recorded. A traditional Chinese syndrome diagnosis is required, and the diagnosis will be documented. Acupuncture treatment will be performed twice a day and lasts for 30 minutes. If the included subjects do not meet the exclusion criteria and do not terminate their participation in study, they will receive acupuncture treatment during their entire ICU stay. If the patient is discharged from the ICU, the acupuncturist will continue to follow the patient until the 14-day acupuncture session is completed. Both the acupuncture group and the control group will receive basic sepsis treatment. The selection of acupuncture points is listed in Table 1.

**Table 1 T1:**
[figure not shown]
. Selection of acupoints and positioning.

#### Basic treatment (Standard of care)

2.5.2

The basic treatment was developed based on the "Surviving Sepsis Campaign: International Guidelines for Management of Sepsis and Septic Shock: 2016”.^[22]^ According to those guidelines, targeted blood glucose range will be set between 8-10 mmol/L (90-144 mg/dL),^[23]^ sedative drugs will be ceased as soon as possible, the use of neuromuscular blockers will be restrain, and early physical exercise will be encouraged.^[23]^

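### The standard-care blood-glucose target is printed as two ranges, 8-10 mmol/L and 90-144 mg/dL, that are not equivalent and meet only at about 8 mmol/L

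*Protocol article*

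**What the plan says.** Section 2.5.2 (Basic treatment) of the protocol article describes standard care for sepsis and includes a glucose target: "targeted blood glucose range will be set between 8-10 mmol/L (90-144 mg/dL". The mmol/L range comes first, the mg/dL range follows in parentheses as its conversion, and a literature citation is attached.

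Section 2.5.1 (Acupuncture treatment) makes clear who receives this care: "Both the acupuncture group and the control group will receive basic sepsis treatment". The target therefore covers all 98 planned patients.

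Section 2.8.6 (Collecting healthcare data within the ICU stay) lists items recorded for patients discharged alive from the ICU, among them "statin dose, blood glucose level, insulin dosage, glucocorticoid dosage". It gives no target and no unit, so it is context here and not a second place where the error occurs.

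No other part of the article that is shown gives a glucose target or says which unit governs. The body of Table 3, the bedside protocol, is not shown.

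**The concern.** A parenthesis after a measured quantity tells the reader that the same quantity is being restated in other units. Here the two figures describe different concentrations. Someone working in mmol/L and someone working in mg/dL would take different targets from the same sentence, and almost any reading that satisfies one would fail the other.

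What is at stake is the care of critically ill patients, because this is a stated treatment threshold and not background text. There is a lesser point about interpretation: glucose and insulin dose are recorded, and a later reader could not tell from the article which target those values should be judged against.

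**Working it through.** **Inputs.** From section 2.5.2: 8 and 10 mmol/L; 90 and 144 mg/dL. The conversion factor is not in the article. It is a physical constant: the molar mass of glucose is about 180.16 g/mol, so 1 mmol/L is about 18.016 mg/dL. Values of 18.0, 18.016 and 18.0182 were tried to cover the usual rounding.

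**Step 1: can the printed equivalence be reproduced?** Dividing each mg/dL limit by the mmol/L limit it is paired with gives the factor that the text implies:

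- lower limits: 90 / 8 = 11.25
- upper limits: 144 / 10 = 14.4

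Neither is 18, and they differ from each other. No single conversion factor links the two ranges, so the printed figure cannot be reproduced.

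**Step 2: convert each range** (mg/dL = mmol/L × factor).

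| Factor | 8-10 mmol/L in mg/dL | 90-144 mg/dL in mmol/L |
|---|---|---|
| 18.0 | 144.0-180.0 | 5.000-8.000 |
| 18.016 | 144.13-180.16 | 4.996-7.993 |
| 18.0182 | 144.15-180.18 | 4.995-7.992 |

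**Step 3: overlap.** With factor 18.0 the ranges share the single point 8.0 mmol/L = 144 mg/dL. With 18.016 or 18.0182 the mg/dL range ends just below 8 mmol/L (7.993 or 7.992), so strictly they do not overlap at all. For practical purposes they touch at one boundary.

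**Step 4: size of the gap** (factor 18.0).

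- Lower limits: 8 - 5 = 3 mmol/L, which is 144 - 90 = 54 mg/dL.
- Upper limits: 180 - 144 = 36 mg/dL, which is 10 - 8 = 2 mmol/L.

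**Step 5: what this means for a single reading.**

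- 6 mmol/L = 6 × 18 = 108 mg/dL: within the mg/dL range, below the mmol/L range.
- 9 mmol/L = 9 × 18 = 162 mg/dL: within the mmol/L range, above the mg/dL range.

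The arithmetic shows that the ranges disagree. It does not show which was intended.

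**The case against.** The conversion error itself has no good defence. Rounding does not account for it, and the figures stand in running prose, not in a table that might have been garbled. The objections concern what follows from it, and most of them stand.

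- **Use in practice.** The trial runs in one 37-bed unit. Staff who work in a single unit of measurement would act on one range only, and the full protocol or ward orders are not shown. So staff could treat to different ranges, but the article does not show that they have done so or will.
- **Bias between groups.** A reader might infer unequal background care, because allocation is not randomised and the treating clinicians know the group. The article does not support that. One sentence covers both groups, and nothing ties the reading of the unit to group. A difference would need the sentence to be read differently by group, and there is no sign of that.
- **Outcomes and analysis.** A reader might also infer that the results are affected. Glucose is not among the primary or secondary outcomes in section 2.8, nor among the covariates given as examples in section 2.10, and the sample size does not depend on it. Recording glucose and insulin means that the control actually achieved can be described afterwards, at least for patients who leave the ICU alive.
- **Other locations.** It would be wrong to count section 2.8.6 as a repeat of the error, since it states no target. It would also be wrong to assume that the bedside protocol carries the error, since its content is not shown.

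None of this removes the contradiction in section 2.5.2. Even if the bedside protocol gives one clear range, that sentence would still disagree with itself.

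**Conclusion.** The point holds as an internal contradiction in a treatment target that applies to every patient. The two printed ranges are about 144-180 and 90-144 mg/dL (about 8-10 and 5.0-8.0 mmol/L), and they share at most the boundary at about 8 mmol/L. This rests only on the glucose conversion factor of about 18, and the conclusion is the same for every value tried.

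The consequence is a patient-safety ambiguity: staff following the sentence could aim for different levels. That is enough to require correction. It is not a demonstrated difference in care between the groups, and it is not a demonstrated effect on any outcome or analysis. The cited source is not available to this review, and no view is taken on which range is right.

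**What to change.** The sponsor should:

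1. Reconcile the two ranges in section 2.5.2 against the source cited there, and print one target with correctly converted units.
2. Check the bedside protocol (Table 3) and, if it states a glucose target, bring it into line.
3. Establish which range was used for patients already treated, and record the answer so that the glucose and insulin data can be read against the target in force.

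The cost is a one-line correction and a notice to staff, plus a short check of unit practice for patients already treated. The design, sample size and analysis need no change on this account.
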